## Abstract

**Background:**

In patients with high risk stage II and stage III colon cancer (CC), curative surgery followed by adjuvant FOLFOX-4 chemotherapy has become the standard of care. However, for 20 to 30 % of these patients, the current curative treatment strategy of surgical excision followed by adjuvant chemotherapy fails either to clear locoregional spread or to eradicate distant micrometastases, leading to disease recurrence. Preoperative chemotherapy is an attractive concept for these CCs and has the potential to impact upon both of these causes of failure. Optimum systemic therapy at the earliest possible opportunity may be more effective at eradicating distant metastases than the same treatment given after the delay and immunological stress of surgery. Added to this, shrinking the primary tumor before surgery may reduce the risk of incomplete surgical excision, and the risk of tumor cell shedding during surgery.

**Methods/Design:**

PRODIGE 22 - ECKINOXE is a multicenter randomized phase II trial designed to evaluate efficacy and feasibility of two chemotherapy regimens (FOLFOX-4 alone and FOLFOX-4 + Cetuximab) in a peri-operative strategy in patients with bulky CCs. Patients with CC deemed as high risk T3, T4 and/or N2 on initial abdominopelvic CT scan are randomized to either colectomy and adjuvant chemotherapy (control arm), or 4 cycles of neoadjuvant chemotherapy with FOLFOX-4 (for *RAS* mutated patients). In *RAS* wild-type patients a third arm testing FOLFOX+ cetuximab has been added prior to colectomy. Patients in the neoadjuvant chemotherapy arms will receive postoperative treatment for 4 months (8 cycles) to complete their therapeutic schedule. The primary endpoint of the study is the histological Tumor Regression Grade (TRG) as defined by Ryan. The secondary endpoints are: treatment strategy safety (toxicity, primary tumor related complications under chemotherapy, peri-operative morbidity), disease-free and recurrence free survivals at 3 years, quality of life, carcinologic quality and completeness of the surgery, initial radiological staging and radiological response to neoadjuvant chemotherapy, and the correlation between histopathological and radiological response. Taking into account a 50 % prevalence of CC without *RAS* mutation, accrual of 165 patients is needed for this Phase II trial.

**Trial Registration:**

NCT01675999 (ClinicalTrials.gov)

## Background

With about 1 million new cases in developed countries annually and 500 000 annual deaths, colon cancer (CC) is the second leading cause of cancer death in Western countries and a significant public health issue [1]. Curative treatment of CC, possible in nearly 80 % of cases, is based on carcinologic surgical resection. For stage III CC (any T/N1-2/M0), adjuvant FOLFOX-4 chemotherapy for 6 months is the standard of care. In the MOSAIC trial [2] that compared adjuvant LV5FU2 with FOLFOX-4 in 2246 stage II and III CC patients, there was a significant increase in disease-free survival at 3 years in the FOLFOX-4 group (78.2 % vs. 72.9 %, for all patients combined; 72.2 % vs. 65.3 % for the stage III subgroup). The 5 % difference in events at 3 years (26.1 % vs. 21.1 %) resulted in a hazard ratio (HR) of 0.77 corresponding to a 23 % risk reduction for patients receiving oxaliplatin. These results were confirmed at 4- and 6-years [3, 4]. For stage II CC (T3-4/N0/M0), the benefit of adjuvant chemotherapy remains controversial and there is a significant heterogeneity in patients outcome within this stage. In the MOSAIC study, high risk stage II patients defined as N0/M0 patients with a T4 primary tumor, bowel obstruction, tumor perforation, poorly differentiated tumor, tumors with satellite venous or lymphatic invasion, or less than 10 lymph nodes examined, a non-significant gain of 3 % in disease-free survival at 3-years was observed for the FOLFOX-4 arm compared with the LV5FU2 arm (HR: 0.72 [0.48-1.08]) [5]. The published QUASAR 2 study [6] compared adjuvant 5-FU plus Folinic Acid ± Levamisole with no adjuvant chemotherapy in 3,239 patients with colorectal cancer (92 % stage II in a mixed population of 71 % colon and 29 % rectal cancer). The results showed an absolute gain of 2.9 % in overall survival at 5-years for the chemotherapy group for the entire population (p = 0.02, and for stage II, p = 0.04). The absolute benefit of adjuvant chemotherapy in stage II CC patients is generally considered between 2 and 5 %. Therefore, it is currently recommended that adjuvant therapy shall be discussed on a case-by-case basis, considering the risk-benefit ratio for each patient resected from a stage II disease, with strong consideration given to patients with high risk stage II CC as defined previously [7, 8].

The 20 to 30 % risk of local or distant recurrence observed in patients with stage II/III, non-metastatic CC operated in a curative intent and receiving adjuvant chemotherapy reflects the relative failure of such a strategy to prevent the risk of locoregional spread of tumor cells or eradicate distant micrometastases. Several reasons may explain this failure: the delayed start (up to 4 months) of chemotherapy after the initial diagnosis and the rapid doubling time of colorectal metastases, which may progress during this time interval without chemotherapy [9]. The stimulation of growth factors related to the operation and the immunosuppression induced during the immediate postoperative period are two other factors that may promote the growth of micrometastases and tumor progression in the postoperative setting [10–12]. The initiation of a neoadjuvant chemotherapy in these patients could improve prognosis by controlling these potential deleterious factors and improving the completeness and the quality of the cancer surgery by local "down-staging,” and by eradicating circulating micrometastases. Neoadjuvant chemotherapy could also test the response of the tumor and thus its chemo-sensitivity; and when appropriate, adjuvant chemotherapy may be adapted.

The potential benefit of such a peri-operative strategy in stage II/III CC is strengthened by: i) recent advances in radiology, which allows a good prediction of tumor stage (wall penetration and nodal involvement) prior to surgery [13, 14]; ii) the histological response observed in primary colon tumors treated by systemic chemotherapy [15] and iii) the demonstrated benefit of combining pre- and postoperative chemotherapy and/or radiotherapy in various gastrointestinal tumors (oesophageal, gastric, rectal and colorectal liver metastases) by several randomized trials [16–18].

## Methods/Design

### Protocol overview

The Prodige 22 - ECKINOXE trial is a multicenter randomized phase II trial designed to evaluate efficacy (response rate) and feasibility (safety, tolerability) of two chemotherapy regimens (FOLFOX-4 alone and FOLFOX-4 + Cetuximab) in a peri-operative setting in patients with stage II/III CC. Control arm includes patients for whom standard treatment comprises surgery followed by adjuvant FOLFOX-4 chemotherapy. This phase II study will assess the feasibility of a peri-operative strategy in these patients and the impact of adding cetuximab in this setting for patients with *RAS* wild type tumors.

A double central, independent and blinded review of imaging and pathology is planned. All eligible patients will be randomized to either surgery alone or neoadjuvant chemotherapy with simplified FOLFOX-4. Patients randomized to the simplified FOLFOX-4 arm will be randomized to receive Cetuximab or not if they are *RAS* WT

Thus based on the *RAS* status of the primary tumor the design will be: Arm A vs. Arm B vs. Arm C for *RAS* WT patients and Arm A vs. Arm C for those *RAS* mutated (Fig. 1)

Arm A: simplified FOLFOX-4 alone every 2 weeks for 4 cycles, followed by colectomy, followed by simplified FOLFOX-4 alone every 2 weeks for 8 cycles.

Arm B: Cetuximab plus simplified FOLFOX-4 every 2 weeks for 4 cycles, followed by colectomy, followed by Cetuximab plus simplified FOLFOX-4 every 2 weeks for 8 cycles.

Arm C (control arm): Colectomy followed by simplified FOLFOX-4 alone every 2 weeks for 12 cycles. Adjuvant chemotherapy will be given to all patients with stage III CC and according to the local practices for stage II cancer.

**Fig. 1 Fig1:**
[figure not shown]
Protocol overview. Temporal sequence of trial conduct in patients with *RAS* WT colon tumor (1A) or RAS mutated colon tumor (1B)

### Inclusion criteria

For inclusion in the study, all of the following inclusion criteria must be fulfilled: (i) pathologically confirmed colon adenocarcinoma (≥15 cm from the anal verge); (ii) assessment of *RAS* status of the primary colon cancer on biopsies (WT or mutated); (iii) CC classified by abdominal CT scan: high risk T3 (disruption of muscle wall and extension into pericolic fat with more than 5 mm protrusion into adjacent mesenteric fat) - T4 (penetration within adjacent organs) and/ or N2 (more than 3 clustered lymph nodes above 1 cm in shortest diameter); (iv) non metastatic CC (lung, liver, peritoneal); (v) non complicated primary tumor (obstruction, perforation, bleeding). Patients with obstructive CC and treated by defunctioning stoma can be included; (vi) absence of synchronous colorectal cancer ; (vii) age ≥ 18 years et ≤ 75 years; (viii) ECOG performance status 0–1 ; (ix) no prior chemotherapy or abdominal or pelvic irradiation; (x) life expectancy of ≥ 5 years; (xi) no history of colorectal cancer; (xii) patients with childbearing potential should use effective contraception during the study and the following 6 months; (xiii) laboratory data including : white blood cell count ≥ 3 × 10^9^/L with neutrophils ≥ 1.5 × 10^9^/L, platelet count ≥ 100 × 10^9^/L, hemoglobin ≥ 9 g/dL (5,6 mmol/l), total bilirubin ≤ 1.5 × ULN (upper limit of normal), ASAT and ALAT ≤2.5 × ULN, Alkaline phosphatase ≤1.5 × ULN, serum creatinine ≤ 1.5 × ULN; (xiv) signed written informed consent obtained prior to any study specific screening procedures.

### Exclusion criteria

Patients are not eligible for this study if any of the following exclusion criteria apply: (i) contra-indication to iodinated contrast medium injection including allergy to iodinated contrast medium and renal insufficiency proscribing iodinated injection; (ii) rectal cancer located within 15 cm from the anal verge by endoscopy or under the peritoneal reflection at surgery or having received radiation therapy prior to surgery; (iii) complicated primary CC (obstruction, bleeding, perforation); (iv) synchronous colorectal cancer; (v) metastatic spread at baseline assessment (lung, liver, peritoneal); (vi) history or current evidence on physical examination of central nervous system disease or; (vii) peripheral neuropathy ≥ grade 1 Common Toxicity Criteria for Adverse Events (CTCAE) v.3.0; (viii) known hypersensitivity reaction to any of the components of study treatments; (ix) presence of inflammatory bowel disease; (x) HNPCC syndrome or polyposis; (xi) major surgical procedure, open biopsy or significant traumatic injury within 28 days prior to study treatment start. Incompletely healed wounds or anticipation of the need for major surgical procedure during the course of the study; (xii) clinically relevant coronary artery disease or history of myocardial infarction in the last 12 months, or high risk of uncontrolled arrhythmia; (xiiii) pregnancy (absence to be confirmed by ß-hCG test) or breast-feeding period; (xiv) previous malignancy in the last 5 years; (xv) medical, geographical, sociological, psychological or legal conditions that would not permit the patient to complete the study or sign informed consent; (xvi) any significant disease which, in the investigator’s opinion, would exclude the patient from the study.

### Endpoints

By evaluating two chemotherapy regimens in patients with *RAS* WT tumor (FOLFOX-4 vs. FOLFOX-4 – Cetuximab), the present trial will determine which neoadjuvant regimen is the most efficient in terms of response rate in patients with non metastatic locally advanced CC.

The primary objective is to assess the histopathological response to neoadjuvant chemotherapy measured by the Tumor Regression Grade (TRG), as simplified to three categories by Ryan [19]. The TRG-Ryan is based on the relationship between fibrosis and the amount of residual tumor cells is defined as follows (Fig. 2). The histopathological finding of fibrous stroma containing few viable tumor cells can be naturally present in almost 10 % of CCs not treated with chemotherapy prior to surgery [15]. Therefore, this parameter represents an objective measure of evaluation in the control (no pre-operative chemotherapy) and study (neoadjuvant chemotherapy) arms. This limits the risk of wrongly concluding therapy efficacy, thereby meeting the methodological standards of a Phase II randomized study. The histopathological response to neoadjuvant chemotherapy will be centrally assessed by 2 of the 3 members of our Central Review Committee of Pathologists who will be blinded to the patients’ treatment. The objective of the blinded comparison of TRG by two independent pathologists is to assess: (i) the inter-observer reproducibility of this grading system in CC after neoadjuvant chemotherapy; (ii) the specificity of histological "regression" criteria by comparing, without knowing the treatment arms, the histological features of tumors operated on immediately versus that of tumors treated by neoadjuvant chemotherapy.

**Fig. 2 Fig2:**
[figure not shown]
The Tumor Regression Grade (TRG), as simplified to three categories by Ryan (19). TRG1: Major response; TRG2: Intermediate response; TRG3: No response

Secondary endpoints are the following: (i) postoperative morbidity (occurring within 60 postoperative days) graded 0 to 5 according to the Clavien-Dindo classification [20]. If grade 3 or 4 complications occur at a rate ≥ 10 % in either neoadjuvant chemotherapy arm, the arm will be declared hazardous (see section statistical analysis); (ii) the safety of neoadjuvant therapy will be assessed by the systematic collection of toxicity data related to chemotherapy, the total number of cycles administered pre-operatively (documenting reasons for early termination), and the systematic collection of GI symptoms. In addition, complications related to the in situ tumor that could delay the date of surgery or require emergency colonic surgery or stenting, will be documented. These parameters will be evaluated after administration of the first cycle of neoadjuvant chemotherapy; (iii) Regression-free survival at 3-years defined as the time interval between the date of randomization and the date of first recurrence (local, regional or metastatic) or date of death (all causes) if no recurrence; (iv) Disease-free survival at 3 years defined as the time interval between the date of randomization and the date of first recurrence (local, regional or metastatic), or second cancer, or the date of death without recurrence (all causes) and date of second cancer; (iv) Quality of life (evaluated using the EORTC quality of life (QoL) QLQ-C30 and QLQ-CR29); Quality of life will be assessed at the inclusion, after neoadjuvant chemotherapy, at 1 month after surgery and every 6 months thereafter. The QLQ-C30 consists of 30 items with both multi-items scales and single item measures. The internal validation of QLQ-C30 allowed to identify 15 scales and to generate 15 scores: 5 scores of functional scale (physical functioning, role functioning, cognitive functioning, emotional functioning, social functioning), a global health status scare, a financial difficulties scale and 8 symptoms scale (fatigue, nausea/ vomiting, pain, dyspnoea, insomnia, appetite loss, constipation, diarrhoea). These scores vary from 0 (worse) to 100 (better) for functional and global health scale and from 0 (better) to 100 (worse) for symptoms scales. Targeted QoL dimensions for this trial are Global Health, physical and emotional functioning, fatigue and pain of QLQ-30 as well as dimensions of CR29. A 5 points difference in QoL is considered as minimal clinically important difference (MCID). Time to QoL deterioration will be defined as time interval between randomization and first decrease in QoL score greater or equal to 5 points. Patients without QoL decrease greater or equal to 5 points will be censored at the last follow-up. (v) Quality and completeness of the surgical excision evaluated on pathological criteria (number of lymph nodes examined, the completeness of removed mesocolon, surgical margins); (vi) radiological staging and radiological response. The initial radiological staging based on abdominopelvic CT scan will be compared with the histopathological pTNM staging in the control group. CT scan images will be interpreted by the individual study centers, and reviewed by 2 of the 3 members of our Central Review Committee of Radiology. This dual independent reading will assess inter-observer reproducibility of the radiological response to treatment with a test of concordance. The radiological response will be defined by RECIST (v1.1) [21] on CT scan and evaluated in the neoadjuvant chemotherapy arms. These criteria will be applied to the primary colon tumors (largest diameter) and lymph nodes (smallest diameter). The sum of the diameters of the target lesions will be determined on the pretreatment CT scan (initial staging) and compared with the sum of these measures on the reevaluation CT scan (performed within 3 weeks after the completion of neoadjuvant chemotherapy). Interpretation of the reevaluation CT scan will be centralized and carried out independently by 2 of the 3 members of our Central Review Committee of Radiologists blinded to the pretreatment CT scan staging. This dual independent reading will assess inter-observer reproducibility of RECIST criteria applied to CC, and determine if there is a difference in radiological response between the two chemotherapy regimens under investigation in the study; (vii) Correlation between histopathological and radiological response. The radiological response of the primary tumor as defined by RECIST v1.1 criteria (taken for target lesion, only the primary tumor) will be compared with the histopathological response as defined by TRG-Ryan. Evaluation of this correlation will be centralized and carried out by the Central Review Committee of Radiology and Pathology; (viii) The 5-point regression grading system [22] adapted to CC by our team in a pilot study [15], will also be evaluated in this trial. This assessment will be centralized and carried out independently and blindly (without knowing the treatment arms) by 2 of the 3 members of our Central Review Committee of Pathology. This assessment will determine the inter-observer reproducibility of this grading system in CC after chemotherapy and to assess the specificity of histological "regression" criteria using this grading system. Comparison of the reproducibility (test of concordance) of the two systems of grading regression (TRG-Ryan and TRG-Mandard) will identify the most appropriate system for assessing response to chemotherapy in CC.

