### Statistical analysis and sample size

Patients RAS Wild Type will be randomized between arm A, B and C whereas RAS mutated patients will be only randomized between arm A and arm C. According to Simon (Optimax) 2 steps design, it will be required to include 33 patients/ arm (with unilateral alpha type one error of 5 % and a power of 95 %) to test following hypotheses: (i) H_0_: an histological response (TRG1-Ryan) rate of 10 % is uninteresting; (ii) H_1_: an histological response (TRG1-Ryan) higher than 10 % is required to rate pursue investigations in phase III trial. A response rate of 35 % is expected.

At the first step (interim analysis), after inclusion of the first 13 patients in each arm, if the number of histological response (TRG1-Ryan) is ≤ 1, inclusion in this arm will be stopped and if the number of histological response (TRG1-Ryan) is ≥ 2, inclusion of the next 20 patients will be done. Calculated power at the interim analysis is 97 %.

At the 2^nd^ step (final analysis), after inclusion of 33 patients in each arm, if the number of histological response (TRG1-Ryan) is ≤ 6, this arm will be declared uninteresting for further investigations in phase III trial and if the number of histological response (TRG1-Ryan) is ≥ 7, this arm will be declared interesting for further investigations in phase III trial. At the second step calculated power will be 96.3 % and alpha type one error will be 2 %. In control arm no interim analysis is plan for efficacy. Then in this arm, at the second step, calculated power will be 97.2 % and alpha type one error will be 4.2 %. If ≥ 10 % of complications ≥ grade III (Clavien and Dindo classification) within 60 postoperative days are reported, this arm will be declared unsafe.

Interim and final results of this phase II study will be reviewed by an independent data monitoring committee (IDMC). Trial will be pursued in phase III with 2 or 3 arms according to IDMC recommendations. Control arm (no neoadjuvant treatment) will be kept as control arm in phase III whatever the results of phase II study. Required number of patients is 33 × 3 = 99 patients for RAS WT patients and 33 × 2 = 66 for those with RAS mutated. Taking into account prevalence of RAS WT patients of 50 %, it will be necessary to screen 192 patients to obtain 99 patients RAS WT and 66 patients mutated for RAS with a minimal probability of 90 %.

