### Ethics and safety

This study protocol was approved by the Institutional Review Board, the Ile de France IX ethic committee on November 2011 and the AFSSAPS (Agence Française de Sécurité Sanitaire des Produits de Santé) on September 2011 under the registration number A110936-41. The institutional promoter is the Assistance Publique Hôpitaux de Paris, France. The trial has been registered on ClinicalTrial.gov website under the identification number NCT01675999. This study received a grant from the French National Cancer Institute (INCA) in 2010. The study complies with the Declaration of Helsinki rules and the principles of the Good Clinical Practices guidelines. Informed consent will be obtained from each patient in a written form prior to randomisation. Patient safety and all potential threats to the patients will be monitored every 6 months by an independent data safety monitoring board (DSMB) and, additionally, at the discretion of the DSMB or Promoter. The DSMB also will evaluate the primary endpoint data. Qualified personnel at the sponsor site will also meet every three months to review safety data, including adverse events and serious adverse events. Any information deemed to potentially affect the safety of the trial will be brought to the attention of the DSMB. An Independent committee (IDMC) including at least 1 clinicien, 1 methodologist and pharmacologist will be created before trial initiation. This IDMC should statute on efficacy and safety at the interim analysis regarding decision criteria of Simon design, post operative morbidity.

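### The endpoint text counts only grade 3 or 4 complications towards the arm-level safety rule, while the statistical section it refers to counts grade III or higher, which includes grade 5

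*Protocol article*

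**What the plan says.** The Endpoints section lists as secondary endpoint (i) "postoperative morbidity (occurring within 60 postoperative days) graded 0 to 5 according to the Clavien-Dindo classification". The next sentence gives the decision rule: "If grade 3 or 4 complications occur at a rate ≥ 10 % in either neoadjuvant chemotherapy arm, the arm will be declared hazardous". It closes with a pointer to the statistical analysis section.

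Statistical analysis and sample size states the rule again. It begins "If ≥ 10 % of complications ≥ grade III", names the same classification, and ends "within 60 postoperative days are reported, this arm will be declared unsafe".

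Both statements use Clavien-Dindo grading, a 60-day window and a 10% limit, and one refers to the other. They are one rule written twice. The article does not say which wording prevails.

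Two other provisions bear on the consequence. The statistical section says "Trial will be pursued in phase III with 2 or 3 arms according to IDMC recommendations". Ethics and safety says "Patient safety and all potential threats to the patients will be monitored every 6 months" by an independent board, and it has the independent committee rule on postoperative morbidity at the interim analysis.

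**The concern.** On a scale that runs to 5, a trigger at grade III or above takes in grades 3, 4 and 5, and a trigger at grade 3 or 4 leaves out the top grade. Grade 5 is conventionally death. The article does not spell that out, but the contradiction stands without it, because the Endpoints section itself gives the scale a grade 5.

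A patient whose only severe event is grade 5 therefore counts towards the rule in one section and not in the other. The rule decides whether a neoadjuvant arm is labelled hazardous or unsafe, so the difference affects a prespecified decision. If the Endpoints sentence were programmed as written, the worst outcome on the scale would not count against the arm.

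**Working it through.** **Inputs from the article.** Limit: 10% or more. Patients per arm: 33 at the final analysis and 13 at the interim (Statistical analysis and sample size). The same section plans 33 × 3 RAS wild-type and 33 × 2 RAS mutated patients. Arm A is open to both groups and would total 33 + 33 = 66 if pooled. The article gives no operating characteristics for the safety rule, so there is no stated figure to reproduce.

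**Trigger counts, read as a proportion of patients.** The smallest whole number reaching 10% of n is:
- n = 13: 2 patients (1/13 = 7.7%, 2/13 = 15.4%)
- n = 33: 4 patients (3/33 = 9.1%, 4/33 = 12.1%)
- n = 66: 7 patients (6/66 = 9.1%, 7/66 = 10.6%)

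**Same data, two decisions.** Each grade 5 patient below has no earlier grade 3–4 complication.

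| Data | Endpoints (grade 3 or 4) | Statistical section (grade III or above) |
|---|---|---|
| 33 patients: three grade 3–4, one grade 5 | 3/33 = 9.1%, not hazardous | 4/33 = 12.1%, unsafe |
| 13 patients: one grade 3–4, one grade 5 | 1/13 = 7.7%, below the limit | 2/13 = 15.4%, above the limit |

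This comparison needs no assumed rates.

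**How often the wordings would disagree: illustration only.** Let p be the proportion of patients with non-fatal grade 3–4 complications, m the proportion with grade 5, and f the share of grade 5 patients with no earlier grade 3–4 complication. None of the three is in the article. With t the trigger count, the probability of disagreement is

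P(X ≥ t | n, p + m) − P(X ≥ t | n, p + (1 − f)m), X binomial.

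Example with n = 33, t = 4, p = 8%, m = 2%, f = 1: P(X ≥ 4) is 0.423 at a rate of 10% and 0.269 at 8%, a difference of 0.154.

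Results for n = 33, with m = 1% / 2% / 3%:

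| p | f = 1 | f = 0.5 | f = 0.25 |
|---|---|---|---|
| 5% | 0.053 / 0.117 / 0.188 | 0.028 / 0.064 / 0.105 | 0.014 / 0.033 / 0.055 |
| 8% | 0.076 / 0.154 / 0.230 | 0.039 / 0.078 / 0.115 | 0.019 / 0.039 / 0.057 |
| 10% | 0.076 / 0.148 / 0.214 | 0.038 / 0.072 / 0.102 | 0.019 / 0.035 / 0.049 |

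These values of p lie close to the 10% limit, where disagreement is most likely. Over the same m and f, the range is 0.4–7.7% at p = 2%, 1.1–11.9% at p = 15% and 0.4–4.4% at p = 20%.

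Arm size moves the result both ways. With f = 1 and m = 2%, going from n = 33 to n = 66 raises it from 0.154 to 0.219 at p = 8% and lowers it from 0.0855 to 0.063 at p = 15%.

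**The case against.** The best defence is that the Endpoints sentence is not free-standing. It sends the reader to the statistical section, where grade 5 counts, and it can be read as a short summary in an endpoint list. In addition, the safety board meets every 6 months, the independent committee rules on postoperative morbidity at the interim, and phase III depends on that committee's advice. A death would be seen. All of this stands and keeps the point minor. It does not remove the contradiction: the cross-reference does not say which text prevails, the Endpoints section is where the endpoint is defined, and a prespecified rule should not depend on a committee overriding its wording.

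It may also be said that a patient who dies has usually had a grade 4 event first and so is counted anyway. That is the role of f above. It reduces the frequency of disagreement, but not to zero unless every such patient has an earlier grade 3–4 event that stays in the count.

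Two stronger readings are tempting.

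- A reader might infer that the Endpoints wording can only ever be the more lenient one. That holds if both statements use patients as the denominator and cover the same arms. The statistical section leaves both unclear: its percentage can be read as a share of complications, and its reference to this arm follows sentences about the control arm. If the denominator were all complications, four severe ones among more than 40 would fall below 10% (4/0.10 = 40), although four patients of 33 exceed the Endpoints limit. The order of the two rules is then not fixed.
- A reader might quote a figure such as 23% as the share of arms wrongly cleared. The article supplies none of the rates behind it.

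**Conclusion.** The contradiction is real and lies in the current text: the two statements of one safety rule differ on whether grade 5 counts. It can reverse the decision for an arm at 4 of 33 patients, or at 2 of 13 at the interim, provided both statements are read as proportions of patients and the grade 5 patient has no earlier grade 3–4 complication. That is the whole of what is shown. The frequency of disagreement is unknown; the calculated percentages rest on assumed rates and on the choice between 33 and 66 patients. The article does not support the conclusion that deaths would go unnoticed, since the statistical section counts grade 5 and two independent bodies review safety. The point is minor, and the wording to correct is the one under Endpoints.

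**What to change.** In the Endpoints section, secondary endpoint (i), replace the grade range in the decision rule with: *complications of grade 3 or higher (including grade 5)*. Leave the statistical section, the 10% threshold and the sample size unchanged.

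The cost is one phrase. Grades 0 to 5 are already recorded within 60 postoperative days, so no additional data are needed.
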